## Methods

### Study Design and Phases

The S4R project applies an exploratory, longitudinal, mixed-methods co-design methodology to achieve the intended project results, outcomes, and impacts [12] (see Figure 2). It comprises 4 phases and 5 main work packages (WPs):

Input phase (WP1 and WP2)Co-design of the S4R Toolbox and prototype testing phase (WP3)Implementation, evaluation, and finalization phase (WP4)Output phase (WP5)

The choice of methodology is based on and aligned with the project objectives of developing, implementing, and evaluating a research-based toolbox to support leaders. The process will be based on the Medical Research Council’s (MRC) guidelines [13] for developing, implementing, and evaluating complex interventions to improve health care. This framework emphasizes the importance of context, including adaptation to local settings, to ensure success in practice.

The countries included in the project were selected because they organize health care services differently, allowing the S4R Toolbox to be tested under varying conditions. As such, the objective is not to compare outcomes across countries but rather to ensure a positive impact (measurable, observable, or experienced improvements in the resilience and mental well-being of health care workers in older adult care, supported by strengthened leadership practices and improved working conditions) in each setting. The test sites in each country will be recruited to contribute to data collection (interviews and surveys) during the input phase (pretest), toolbox testing, and data collection (interviews, observations, and surveys to enable process evaluation and assess the effectiveness and cost-effectiveness of the toolbox) during the implementation and evaluation phase (posttest). The test sites will include units with a total sample size of 250-500 participants in each country, consisting of health care workers, health care leaders, and informal caregivers. This will provide the basis for pre- to posttest comparisons for test cases 2-4 (see Figure 3). In addition, test case 1 (Norway and Finland) will participate in a cluster randomized controlled trial (cRCT) to assess the effectiveness and cost-effectiveness of the intervention (see Figure 3 for the different test cases).

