**Figure 3 figure3:**
[figure not shown]
Support4Resilience (S4R) test cases in different countries.

Test case 1 will be carried out in Finland and Norway, 2 countries with the most similar older adult care systems (eg, number of older adults receiving care services and home care services), where public home care services are common and are the responsibility of municipalities or counties [14]. Data will be collected, and the S4R Toolbox will be tested in public home care services across a variety of geographical locations (including rural areas), municipalities, and travel distances for health care workers and informal caregivers.

Test case 2 will take place in public residential care institutions and residential care institutions receiving public funding in Spain. Data will be collected, and the S4R Toolbox will be tested in the context of public residential care services. This context is common in several European countries that provide publicly funded residential care services for older adults.

Test case 3 focuses on private residential care in Italy, the Netherlands, and Australia. In Italy, the S4R Toolbox will be tested in a large facility with 450 employees. In the Netherlands and Australia, the S4R Toolbox will be tested in private residential care networks because of the structure of their health care systems. Australia will conduct an independent evaluation because of its complementary Australian funding.

Test case 4 represents the part of Europe where home care services and residential care homes are largely absent. In these settings, families provide care outside hospitals [14]. For this purpose, data will be collected in Romania, and the S4R Toolbox will be tested in an older adult care context representing the hospital-to-home interface. Health care services for older adults in Romania are provided primarily by hospitals, whereas public services to support patients in their homes are limited. Consequently, home care is typically provided by patients’ families. Recruiting a public hospital will therefore enable the project to investigate relevant aspects of older adult care within these types of health care systems.

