#### Resilience and Mental Well-Being Factors Among Health Care Workers, Informal Caregivers, and Leaders

An online survey will be conducted in the 6 European partner countries and Australia. WP2 aims to map resilience and mental well-being factors and explore their associations across 7 health care systems. A total sample of 2500-3000 participants (minimum of 300 leaders, 1000 informal caregivers, and 1200 health care workers) will ensure:

Adequate statistical power for multivariable regression (at least for informal caregivers and health care workers)Sufficient representation of health care workers, leaders, and informal caregiversReliable estimation of psychometric properties, including those of the new RCS.

WP2 is descriptive and exploratory; multivariable regression models will be used to explore associations among resilience, mental well-being, job characteristics, and demographic factors and to inform instrument development and intervention design. These analyses are not intended for confirmatory hypothesis testing. Consequently, no formal power calculation was conducted for WP2. Instead, the sample size was determined based on feasibility, stakeholder representation, and the requirements for psychometric evaluation. Moreover, the limited availability of leaders in older adult care must be taken into account.

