We will assess the effectiveness of the S4R Toolbox through a cRCT (test case 1), a pre-post evaluation (test cases 2-4), and a cost-effectiveness evaluation (test case 1). In both study designs, the primary outcome will be health care workers’ mental well-being, measured using the SWEMWBS. Secondary outcome measures include individual resilience, organizational resilience capacities, burnout, turnover intention, self-assessed health, and, for informal caregivers, family involvement in care and caregiver self-assessment. In addition, sick leave will be assessed using public sick leave records where available. The effectiveness, cost-effectiveness, and cRCT analyses of the S4R intervention will provide information for decision makers in organizations at both the national and European Union (EU) levels.

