#### Pre-Post Evaluation (Test Cases 2-4)

Changes from baseline to postintervention will be examined using mixed-effects regression models. Individuals will be nested within organizational units, with random intercepts included for organizational units. Time will be entered as a fixed effect. Standardized effect sizes (Cohen *d*) will be calculated to aid interpretation.

For countries using a pre-post evaluation, a sample of 250-500 participants per country is sufficient to

Detect moderate changes (effect size, *d*≈0.25-0.36) with 95% power (taking clustering into account, assuming an intraclass correlation coefficient [ICC] of 0.05).Estimate within-country effects using mixed-effects models.Explore relevant subgroup differences.

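### The pre-post power statement counts all 250-500 participants per country, but the primary outcome is measured in health care workers only, so the detectable d of 0.25-0.36 is not supported as written

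*Protocol article*

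**What the plan says.** Three places in the protocol article bear on this.

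- **Study Design and Phases** gives the test sites a "total sample size of 250-500 participants in each country, consisting of health care workers, health care leaders, and informal caregivers". It adds: "This will provide the basis for pre- to posttest comparisons for test cases 2-4".
- **Implementation, Evaluation, and Finalization Phase, Overview** fixes the endpoint: "In both study designs, the primary outcome will be health care workers’ mental well-being, measured using the SWEMWBS".
- **Pre-Post Evaluation (Test Cases 2-4)** states the power: "For countries using a pre-post evaluation, a sample of 250-500 participants per country is sufficient to" and, as the first bullet, "Detect moderate changes (effect size, *d*≈0.25-0.36", with 95% power and an ICC of 0.05.

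The pre-post section gives no number of health care workers, no unit size, no within-person correlation and no alpha. The survey section lists SWEMWBS for workers and leaders, and two other questionnaires for informal caregivers. The cRCT section, by contrast, counts health care workers explicitly (about 30 per cluster, about 9 responding).

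**The concern.** The same 250-500 serves as a three-group total in one section and as the sample behind a power claim in another. The primary analysis can use only the worker part of that total. If the calculation used all of it, the stated detectable change is too favourable for the primary outcome.

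This sentence is the only power justification given for the pre-post design, which covers Spain, Italy, the Netherlands, Romania and Australia (Australia evaluates independently). A reader who relies on it could take a null country result as evidence against a change of 0.25-0.36 when the worker sample may have had less than 95% power to detect one.

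**Working it through.** **Inputs.** From the pre-post section: N = 250-500, power 95%, ICC 0.05. Assumed: two-sided alpha 0.05, so the multiplier is 1.960 + 1.645 = 3.605. Borrowed from the cRCT section, because the pre-post section gives none: 30 workers or 9 respondents per unit, and within-person correlation r = 0.5-0.7.

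**Formula.** Detectable d = 3.605 × sqrt(2(1 − r) × DE / n), with DE = 1 + (m − 1) × 0.05 and m respondents per unit.

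**Step 1: reproduce the stated range with the full total as n.**

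- m = 30 gives DE = 1 + 29 × 0.05 = 2.45; r = 0.5 gives 2(1 − r) = 1.
- n = 250: 3.605 × sqrt(2.45/250) = 0.357.
- n = 500: 3.605 × sqrt(2.45/500) = 0.252.

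An unpaired version (r = 0) also fits: m = 6 (DE = 1.25) gives 0.360 and 0.255, and m = 5 (DE = 1.20) gives 0.353 and 0.250. The ratio 0.36/0.25 = 1.44 is close to sqrt(500/250) = 1.41, which is consistent with n running over the whole stated range.

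**Step 2: keep m = 30 and r = 0.5, and count workers only.** The pre-post design has no stated worker share. The only split printed is for the WP2 survey: a "minimum of 300 leaders, 1000 informal caregivers, and 1200 health care workers", that is 1200/2500 = 48% workers. It is used here as an illustration.

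| Worker share (assumed) | Workers | Detectable d | Power at 0.36 (lower n) and 0.25 (upper n) |
|---|---|---|---|
| 100% | 250-500 | 0.357-0.252 | 95%, 95% |
| 80% | 200-400 | 0.399-0.282 | 90%, 89% |
| 60% | 150-300 | 0.461-0.326 | 80%, 79% |
| 48% | 120-240 | 0.515-0.364 | 71%, 70% |

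If respondents per unit shrink in proportion at the 48% share (m = 14.4, DE = 1.67), the detectable d is 0.425-0.301 and power is 86% and 85%.

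**Step 3: change the unstated inputs.** With m = 9 (DE = 1.40) and r = 0.6, 2(1 − r) × DE = 0.8 × 1.40 = 1.12.

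- 120 workers: 3.605 × sqrt(1.12/120) = 0.348.
- 240 workers: 3.605 × sqrt(1.12/240) = 0.246.

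This meets the stated range with workers only. At r = 0.5 the same workers give 0.389-0.275, and at r = 0.7 they give 0.302-0.213. With the full 250-500, m = 9 and r = 0.6 would give 0.241-0.171, which is not the published range.

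**The case against.** A reader might infer that the design fails to deliver 0.25-0.36 for the primary outcome, and that about 0.36-0.52 is the true figure. The document does not support that, for four reasons.

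- **The inputs are not stated.** The design effect of 2.45 is a back-fit and appears nowhere in the article. The respondents per cluster and base-case design effect that are printed, 9 and 1.40 in the cRCT section, combined with a correlation of 0.6, give about 0.25-0.35 for 120-240 workers.
- **The worker share is borrowed.** The WP2 minima span seven countries, and caregivers in that survey were also recruited through other networks and social media. The mix at the pre-post sites may differ, and a single site could supply many workers: "In Italy, the S4R Toolbox will be tested in a large facility with 450 employees". The 30% response rate belongs to the cRCT and is not applied to the pre-post sites.
- **The inflation may be too strong.** Where the same units are measured twice, a stable unit effect largely cancels from the time contrast. With no inflation and r = 0.5, 120-240 pairs would give 3.605/sqrt(120) = 0.33 to 3.605/sqrt(240) = 0.23.
- **Attrition and detailed inputs** may properly sit in the full plan, and the 250-500 might already mean analysed participants.

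All of this stands against any fixed size for the shortfall. It does not remove the mismatch. The article itself prints the sample, its composition, the primary population and the power figure, and these do not fit together. Even if the 250-500 are analysed participants, they are still defined as three groups. Nothing in the text requires 250 workers in any country. Counting leaders, who also complete SWEMWBS, would raise the illustrative share only to (1200 + 300)/2500 = 60%, and leaders are not named in the primary outcome population.

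**Conclusion.** The power statement is not supported as written for the primary outcome. The mismatch between the three sections is certain. The direction is also certain with other inputs held: any worker share below 100% makes the detectable d larger than the one implied by the full total.

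The size is conditional. On the inputs that reproduce the stated range, it runs from about 0.28-0.40 at an 80% worker share to about 0.36-0.52 at 48%, where power at the stated effects is about 70%. On other plausible inputs, a worker-only sample reaches the stated range. The alpha, unit size, correlation and worker share behind these figures are all assumed or borrowed. It should be fixed, but it does not show that the evaluations are underpowered.

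**What to change.** Restate the first bullet under Pre-Post Evaluation (Test Cases 2-4) for the expected number of health care workers per country with both a pre and a post SWEMWBS. Name the respondents per unit, the within-person correlation and the alpha, and recompute the detectable d or the power from them. Alternatively, define the 250-500 as health care workers only and amend Study Design and Phases to match.

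Do not insert 0.36-0.52 as a replacement, since it rests on a back-fitted design effect and a borrowed worker share.

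The cost is a possibly less favourable stated figure. No extra recruitment is needed if the restated figure is accepted. It is best settled before follow-up data are seen.

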#### cRCT (Norway and Finland; Test Case 1)

The S4R Toolbox will be evaluated in a 2-arm cRCT in 2 countries (Finland and Norway). An equal allocation ratio will be used for the 2 groups: an intervention arm, in which the S4R Toolbox is implemented by health care leaders, and a control arm, in which the S4R Toolbox is not implemented by health care leaders. The cRCT will include 30 clusters with approximately 30 health care workers per cluster. Accounting for clustering (ICC=0.05), an expected 30% response rate (approximately 9 respondents per cluster), and 6 repeated measurements (baseline plus 5 follow-up assessments) with a plausible within-person correlation of 0.5-0.7, the cRCT has 95% power to detect standardized effect sizes of approximately *d*=0.28-0.32 for mental well-being. The 6 measurement time points were chosen to align with the planned phases of Toolbox use and feasible data collection windows in the participating services. This pragmatic schedule enables monitoring of early adoption and engagement, as well as whether changes are sustained over the intervention period.

The sample size calculations assumed an ICC of 0.05 and an average of approximately 9 respondents per cluster (30% response from approximately 30 eligible workers). The assumed ICC of 0.05 was selected based on previous cluster randomized trials in primary care, home care, and organizational intervention studies, in which ICCs for psychosocial and workforce-related outcomes commonly ranged from 0.01 to 0.10. Given the lack of precise prior ICC estimates for mental well-being outcomes in older adult home care services, an ICC of 0.05 was considered a conservative and appropriate planning value. This corresponds to a cluster design effect of 1.40. To assess the robustness of the findings to uncertainty in the ICC, we conducted sensitivity analyses using ICC values of 0.03, 0.08, and 0.10 (design effects of 1.24, 1.64, and 1.80, respectively). Holding all other assumptions constant, the detectable standardized effect size ranged from *d*=0.26-0.30 (ICC=0.03) to *d*=0.30-0.35 (ICC=0.08) and *d*=0.32-0.36 (ICC=0.10), compared with *d*=0.28-0.32 under the base-case ICC of 0.05. These findings indicate that the trial is sufficiently powered to detect small-to-moderate improvements in the primary outcome.

A 30% response rate was used as a conservative planning assumption for this pragmatic workforce trial in older adult care to reduce the risk of overestimating the effective sample size under real-world conditions. Participation and retention will be supported through leadership engagement, brief, mobile-friendly questionnaires, repeated reminders, and monitoring of response rates at each measurement time point.

The primary outcome measure, the SWEMWBS, will be treated as a continuous outcome. The primary analysis will follow the intention-to-treat principle at the home care service (cluster) level. Noncompliance with the intervention may attenuate the observed intervention effect. Linear mixed-effects models will be used, including random intercepts for clusters. Group (intervention vs control) will be included as a fixed effect, and SWEMWBS (mental well-being) will be the primary outcome. Other outcomes (burnout, turnover intention, caregiver burden, etc) will be analyzed as secondary end points.

Analyses will follow the intention-to-treat principle. A complier average causal effect analysis will also be conducted to account for variation in exposure to the intervention.

#### Cost-Effectiveness Analysis

Cost-effectiveness analysis will be conducted only for the cRCT study design (Norway and Finland).

The primary outcome will be SWEMWBS, with effectiveness assessed using the same methods described in the previous section.

The costs of the intervention will be based on the time spent by leaders, health care workers, and researchers implementing the S4R Toolbox. The learning collaboratives support the leaders and are therefore expected to influence the effectiveness of the Toolbox. The cost data will be based on the following:

Minutes that health care workers use the Toolbox (data source: log files from the digital Toolbox).Hours that leaders and health care workers spend in meetings discussing the themes of the Toolbox and planning deimplementation or other workplace changes (data sources: learning collaborative meetings and interviews with leaders).Hours that leaders and researchers spend participating in local learning collaboratives (data source: notes/minutes from the learning collaboratives, including time and participants).The time spent by health care workers, leaders, and researchers will be valued using nationally representative wages and social security contributions.

The time horizon for the analysis is 1 year; therefore, no discounting will be applied. The analysis adopts the perspectives of 2 funders: the participating organizations, which cover the costs of leaders’ and health care workers’ time, and the S4R project funding organization (EU), which covers the costs of researchers’ support for implementing the Toolbox.

We use intention-to-treat based analyses and evaluated the incremental net monetary benefit of the Toolbox compared to no Toolbox ("practice as usual"). We evaluated incremental net monetary benefit (NMB) in comparing the alternatives. NMB is calculated by multiplying the observed effects by the decision-makers’ willingness to pay, λ, for an extra unit of effectiveness, and then subtracting the observed cost [37,38]. As the willingness to pay for one extra unit of effectiveness in SWEMWBS is unstated, we use a range of values.

As a sensitivity analysis, we will use an algorithm to convert changes in SWEMWBS scores into WELLBY (Wellbeing-Adjusted Life Year) units [39-41]. WELLBYs have been monetized and can therefore provide a monetary estimate of effectiveness. This analysis will also provide an opportunity to interpret the results of the cost-effectiveness analysis across the range of willingness-to-pay values.

To further support the robustness of our analysis, we will also conduct a cost-benefit analysis. For this analysis, we will collect data from the participating organizations (work units) on sickness absence (spells and days), staff resignations, turnover, disability pensions, and personnel survey results for the years 2023-2026. Where possible, these measures will be monetized using national recommendations, statistics, reports, and research.

The S4R project does not aim to estimate a single pooled effect across countries. The participating health care systems differ substantially in structure, governance, workforce composition, and the availability of formal older adult care services. Because of this heterogeneity, the project follows the MRC guidance for evaluating complex interventions, which explicitly recommends that evaluation designs be adapted to local feasibility and contextual conditions.

In Norway and Finland, organizational structures allow randomization of home care units, making a cRCT feasible and appropriate for evaluating both effectiveness and cost-effectiveness. In the other participating countries, randomization was not feasible because of organizational differences and the absence of comparable units. For these countries, a pre-post evaluation is methodologically appropriate and enables examination of within-country change. This hybrid approach preserves scientific rigor by using the strongest possible design where feasible while ensuring validity and contextual relevance across diverse older adult care systems.

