#### Sustainability of the S4R Toolbox

The S4R intervention design and Toolbox will be open access through the S4R Resource Bank, which includes self-directed instructions on how to implement the intervention. Furthermore, the infrastructure supporting deployment of the Toolbox will ensure server maintenance for 5 years after project completion. This period will also allow time to implement a successful exploitation strategy.

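### The costing rule counts only people's time, so the trial-year cost of running the online Toolbox is left out of the cost-effectiveness analysis

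*Protocol article*

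**What the plan says.** The Cost-Effectiveness Analysis section of the protocol article opens its costing with a rule: "The costs of the intervention will be based on the time spent by leaders, health care workers, and researchers implementing the S4R Toolbox". Three resource items follow. The first is health care workers' minutes on the Toolbox, read from the platform's log files. The second is "Hours that leaders and health care workers spend in meetings discussing the themes of the Toolbox" and planning the resulting workplace changes. The third is "Hours that leaders and researchers spend participating in local learning collaboratives". All of this time "will be valued using nationally representative wages and social security contributions".

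The same section sets the frame: "The time horizon for the analysis is 1 year; therefore, no discounting will be applied". It takes the viewpoint of two funders. One is "the participating organizations, which cover the costs of leaders’ and health care workers’ time". The other is the EU as project funder, which is assigned the cost of researchers' support. Net monetary benefit (NMB) is the effect multiplied by willingness to pay, minus cost, and the comparison is with practice as usual without the Toolbox.

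The rest of the economic plan adds a conversion of well-being scores to WELLBYs and a cost-benefit analysis of absence, resignations, turnover and similar measures. Neither brings in a platform cost.

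Elsewhere, the article describes the Toolbox as an online platform (The Project's Ambition) that produces reports and graphs from stakeholder questionnaires and uses natural language processing (Tool 1). Under Sustainability of the S4R Toolbox it is open access, and "the infrastructure supporting deployment of the Toolbox will ensure server maintenance for 5 years after project completion".

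**The concern.** A digital intervention cannot be delivered without a running platform. Hosting, maintenance and any technical support in the trial year are inputs to the intervention arm, and the control arm has no counterpart. A rule that admits only hours and wages has no place for them: the log files serve only as a source of minutes, and no non-time input has a unit price.

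The article says that the economic results will inform decision makers at national and EU level, and that cost-effective interventions will be passed to policy makers and leaders. If a real input that differs between the arms is left out, the reported cost-effectiveness leans towards the Toolbox. Varying the willingness to pay or converting to WELLBYs does not correct this, because both act on the value of the effect and not on the cost.

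**Working it through.** The plan states no cost or NMB figure, so there is none to reproduce. The check has three parts.

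**1. Is a platform cost anywhere in the cost base?**

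| Element of the costing | Unit | Platform operation included? |
|---|---|---|
| Workers' use of the Toolbox | minutes | No; logs supply time only |
| Meetings of leaders and workers | hours | No |
| Learning collaboratives, leaders and researchers | hours | No |
| Valuation | wages plus social security contributions | No price for a non-time input |
| Organizations' perspective | staff time | No |
| EU funder's perspective | researchers' support | No |

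**2. Direction of the error.** Let ΔE be the incremental effect per worker, ΔC the incremental time cost per worker, λ the willingness to pay, and c the omitted trial-year platform cost per worker.

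- NMB under the stated rule: λΔE − ΔC
- NMB with the platform cost: λΔE − (ΔC + c)
- Difference: c, whatever the value of λ
- Break-even λ rises from ΔC/ΔE to (ΔC + c)/ΔE, an increase of c/ΔE

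This applies to a perspective only if a funder in that perspective pays c.

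**3. Possible size.** The documents give 30 clusters, equal allocation and about 30 workers per cluster, so the intervention arm has 15 × 30 = 450 workers. The remaining inputs are assumptions: a platform cost of EUR 5,000-30,000 a year, and 2 of 7 equal country shares for Norway and Finland.

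- Low: 5,000 × 2/7 ÷ 450 = EUR 3.2 per worker
- High: 30,000 × 2/7 ÷ 450 = EUR 19.0 per worker

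For scale, assume 10 hours of staff time per worker at EUR 35 an hour, which is EUR 350. Then 3.2/350 = 0.9% and 19.0/350 = 5.4%. Counting researcher hours, as the plan does, would enlarge the denominator and lower these percentages.

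The rise in break-even λ, c/ΔE, for an assumed gain on the SWEMWBS:

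| Assumed gain (points) | Low c | High c |
|---|---|---|
| 0.5 | EUR 6.3 | EUR 38.1 |
| 1 | EUR 3.2 | EUR 19.0 |
| 2 | EUR 1.6 | EUR 9.5 |

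**The case against.** The strongest reply is that the scope is declared. The section names two funders and what each covers, so a reader can see what is counted. How to charge a platform shared by seven countries to the trial in two of them is an allocation choice on which costing plans may differ. An article also commonly leaves an itemised unit-cost list to a fuller plan. This stands in part: allocation does need a decision, and detail may be left out. But the article does not leave the cost base open. It states a rule, and the rule as written excludes platform operation.

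Support is also partly counted already, through researcher hours in the learning collaboratives, and no separate help desk is described. That stands, and any added support item must not count those hours twice.

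Three stronger readings are tempting, and the documents do not support them:

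- A reader might infer that the server commitment contradicts the costing rule. It concerns the five years after the project ends, outside the 1-year horizon. It shows that running costs exist, and leaving those later years out of this analysis is correct.
- A reader might infer that both funders' costs are understated. The Toolbox is open access and no charge to the participating organizations is mentioned, so nothing shows that their trial-year cost is too low.
- A reader might put the omission as high as EUR 67 per worker (30,000/450), or 19% of the assumed EUR 350. That charges the whole seven-country platform to the intervention arms of two countries.

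Finally, nothing shows that a cost-effectiveness conclusion would change. That also stands.

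**Conclusion.** The point holds as a minor one. The stated rule is too narrow for an online intervention compared with no Toolbox, because it leaves out platform operation during the trial year. To the extent that the project funder bears this cost, NMB in the EU or combined perspective is overstated by exactly that amount at every willingness to pay.

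The direction follows from the plan's own NMB definition. The size does not: neither the amount nor the payer is stated. The illustrative EUR 3-19 per worker rests wholly on the assumed annual cost and the equal country split. If no funder in the analysis pays for hosting in the trial year, the stated perspectives are not understated, and the plan need only say so.

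**What to change.** Add a fourth item to the cost list: the trial-year cost of operating and supporting the platform, taken from project accounts and allocated across all participating units, so that the cRCT intervention units carry only their share. State which funder bears it and enter it in that perspective. Exclude researcher support hours already counted through the learning collaboratives. Leave one-off development cost out or report it separately. Show the running cost that future adopters would face after the project only as a scenario, since it lies beyond the 1-year horizon.

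If the team prefers to keep a time-only base case, it should state that platform operation is excluded and why, and give a sensitivity analysis that includes it.

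The price is one extra figure from the accounts, an allocation rule, and a slightly less favourable cost. Trial design, data collection from participants and the effectiveness analysis are unchanged.
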